## Abstract

**Background:**

Tobacco advertising and product promotions have been largely banned in the UK but point of sale (POS) tobacco advertising is one of the few places where tobacco products may be legitimately advertised. POS displays have been shown to increase susceptibility to smoking, experimentation and initiation into smoking. These displays may also influence perceived prevalence of smoking and the perception that tobacco products are easily obtained and are a ‘normal’ product. A ban of POS tobacco advertising was introduced in Scotland in large tobacco retail outlets of over 280m^2^ internal sales floor areas (mainly supermarkets) in April 2013 and will be extended to include smaller tobacco retail outlets in April 2015. However, the impact of POS bans on smoking attitudes, behaviours and prevalence has yet to be determined.

**Methods/design:**

This study has a multi-modal before and after design and uses mixed methods to collect data, at baseline and then with longitudinal follow-up for 4 years, in four purposively selected communities. For the purposes of the study, community is defined as the catchment areas of the secondary schools selected for study. There are four main components to the on-going study. In each of the four communities, at baseline and in follow-up years, there will be: mapping and spatial analyses of tobacco retail outlets; tobacco advertising and marketing audits of tobacco retail outlets most used by young people; cross-sectional school surveys of secondary school pupils; and focus group interviews with purposive samples of secondary school pupils. The tobacco audit is supplemented by interviews and observations conducted with a panel of tobacco retailers recruited from four matched communities.

**Discussion:**

This study examines the impact of the implementation of both a partial and comprehensive ban on point of sale (POS) tobacco advertising on attitudes to smoking, brand awareness, perceived ease of access to tobacco products and youth smoking prevalence. The results will be of considerable interest to policy makers both from the UK and other jurisdictions where they are considering the development and implementation of similar legislation.

## Background

Tobacco advertising and marketing activity have been shown to have a direct impact on adolescent smoking intentions, perceived smoking prevalence and youth smoking prevalence [1,2]. In addition, a dose–response relationship has been demonstrated between adolescent tobacco marketing awareness and smoking uptake [3]. Following an EU directive [4], the Tobacco Advertising and Promotion Act (TAPA) was implemented in the UK between 2003 and 2005 [5]. The legislation bans advertising on billboards, in cinemas and print media, by direct mail, on-pack promotions, and through brand sharing and international tobacco sponsorship. On 29^th^ April 2013, point of sale (POS) tobacco advertising was banned in large retailers in Scotland [6]. POS advertising in smaller retail outlets is now one of the few ways in which the tobacco industry can legitimately promote their products in Scotland. The ban will be extended to include these retail outlets in April 2015 [6]. The gantries currently used to display tobacco products are usually supplied by the tobacco industry and sited in prominent in-store positions, most often at checkouts, with products arranged attractively and sometimes positioned in such a way as to obscure health warnings [7]. Recent UK research [8,9] and a systematic review [10] have found that, in children, POS displays increase susceptibility to smoking, experimentation and initiation into smoking. These displays may also influence perceived prevalence of smoking and the perception that tobacco products are easily obtained and are a ‘normal’ product. Studies of adults suggest that POS advertising increases impulse cigarette purchases [11]. Positioning of POS displays may also be important in that cigarette retailers located in communities with a high proportion of children have been shown to be more likely to display cigarettes near children’s products [12]. A multi-centre Canadian study also found that stores near schools with high smoking prevalence had significantly lower mean price per cigarette, more in-store promotions (price, gift or bonus promotions) and fewer government-sponsored health warnings [13].

There are a growing number of jurisdictions, such as Ireland, Iceland, Thailand, and some provinces and territories in Canada [14], where POS bans have been introduced but few studies of the impact of POS bans have been conducted. An exception is a study of the Irish legislation [14], which found that high levels of compliance (97%) were accompanied by increasing support for the law, a reduction in recall of displays among both adults (49% to 22%; p < 0.001) and young people (81% to 22%; p < 0.001), a reduction in perceived youth smoking prevalence among young people, and an increase in beliefs that the law made it easier for adults to quit smoking or for children not to initiate smoking. The study failed to find a reduction in smoking prevalence either among young people or adults. However, the short follow-up period (one month) and the small sample sizes, particularly for young people (n = 214), made it unlikely that a reduction in smoking prevalence would be detected and prevents any conclusions about the longer-term impacts of the Irish legislation being drawn.

### Study aims

In this study we assess the impact of Scottish legislation to ban point of sale (POS) tobacco advertising on young people’s exposure to tobacco advertising, their attitudes towards smoking and their smoking behaviour. We will also identify any ‘unintended consequences’ associated with the implementation of the legislation.

### Intervention

The intervention to be evaluated is the prohibition of tobacco advertising at point of sale (POS) contained in Sections 1 to 3 of the Tobacco and Primary Medical Services (Scotland) Act 2010 (TPMS Act) [6]. The legislation prohibits the display of tobacco products or tobacco-related products in places where tobacco products are offered for sale and requires retailers to conceal cigarettes from general view, either by covering up cigarette gantries/dispensers or by storing cigarettes under the counter. Under the legislation, displays of tobacco products or tobacco-related products (Section 2) and prices (Section 3) are also considered to be advertisements. The overall policy objective of the legislation is to reduce the attractiveness of tobacco products among children and adolescents under the age of 18, which in turn may lead to a reduction in initiation into smoking and in the longer term a reduction in smoking prevalence. The legislation was implemented in large retail outlets (mainly supermarkets) with over 280m^2^ of internal floor area used for the display of goods and serving of customers on 29^th^ April 2013 and will be extended to the remaining smaller tobacco retail outlets in April 2015.

### Research questions

Our specific research questions are:

1. Does implementation of POS regulations in the TPMS Act in i) supermarkets alone (partial ban); and ii) all tobacco retailers (complete ban) result in changes in exposure to tobacco advertising in young people aged 12 to 17 years?

2. Is a reduction in exposure to POS advertising associated with: changes in brand awareness; perceived accessibility of tobacco; perceived prevalence of youth smoking; susceptibility to smoking; and the incidence and prevalence of smoking in young people aged 12 to 17 years?

3. Is there any evidence of socio-economic patterning in any of the attitudinal or behavioural outcomes in young people?

4. What is the association between area-level deprivation and i) levels of POS tobacco advertising and availability of cigarettes pre-and post-legislation; or ii) enforcement of the legislation when implemented?

5. Is there any evidence of a dose-response relationship between changes in exposure to POS advertising and interim and longer-term outcome measures in young people?

6. Are there any unintended adverse consequences associated with the legislation, for example, an increase in cigarette purchases from black-market sources?

7. Is there any evidence of changes in POS advertising and marketing strategies in the lead up to implementation of measures in the TPMS Act in either supermarkets or small retailers?

## Methods/design

The study has a multi-modal before and after design and uses mixed methods to collect data in four purposively selected communities. For the purposes of the study, community is defined as the catchment areas of the secondary schools selected for study. Schools were purposively selected to reflect two levels of urbanisation (large urban vs. small town) and two levels of socio-economic deprivation (high vs. medium or low). Deprivation categories were derived from the population-weighted mean Scottish Index of Multiple Deprivation (SIMD) score for all data zones falling within the school catchment areas and the proportion of children from each school receiving free school meals. To keep the influence of school factors, other than urbanisation and deprivation, to a minimum, the selected schools were non-denominational local authority schools on mainland Scotland with an ethnic minority population of less than 10% of the school roll. In addition, schools were also selected to have a pupil roll of between 1100 and 1200.

There are four main components to the study. In each community we are conducting:

•Mapping and spatial analysis of the location and density of tobacco retail outlets.

•Tobacco advertising and marketing audits of tobacco retail outlets most used by young people, supplemented by interviews and observations with a panel of retailers in four matched communities.

•Cross-sectional school surveys of pupils, with five embedded pupil cohorts.

•Focus group interviews with purposive samples of pupils.

Data for the study components were collected at baseline between February and April 2013, prior to implementation of the legislation on 29^th^ April 2013. Follow-up data collection will be repeated annually for four years. Additional marketing audits were conducted immediately post-legislation in May 2013 to assess compliance in large retail outlets and this will be repeated in May 2015 in smaller retail outlets, following implementation of the POS legislation in smaller retailers in April 2015.

Details of the study components are as follows:

1. Annual mapping and spatial analysis studies of tobacco retail outlets

Data (including address and full postcode) for all tobacco retailers in the study communities were extracted from the tobacco retailers register (http://www.tobaccoregisterscotland.org) and mapped at baseline (January 2013) and then verified through field visits during which every street in the four communities was inspected [15].

Baseline tobacco outlet data were geo-coded (using Code-Point®) to provide geographical coordinates and then integrated into a Geographical Information System (GIS). These data will be combined with data from the marketing audits (see below) and analysed to provide an assessment of changes in tobacco retailing and advertising over the study period. In the analysis of POS exposure, we will limit our focus to supermarkets, off-licences and retailers most likely to sell cigarettes to young people, including confectioners, tobacconists and newsagents, grocers (including licensed), petrol stations, and fish and chip shops.

The data from the mapping and spatial analysis studies will be used to:

•Monitor the number and rate (per population) of tobacco outlets in each of the four communities at baseline and in follow-up years.

•Examine whether there is geographical clustering of tobacco outlets around secondary schools and whether there are changes in clustering over the study period. Using methods trialed by one of the research team (JP) in previous work [16], we will examine the spatial clustering of tobacco outlets within 1.5 km of each school.

•Develop tobacco retailing and advertising exposure measures for each secondary school pupil participating in the study based on a weighted average of tobacco outlets in the buffer surrounding their school and home environments and exposure index scores calculated for each retail outlet using baseline audit data. Mean density estimates will be calculated for 1.5 km buffers around the school and home environment of each secondary school participant.

•Calculate changes in exposure to tobacco products and advertising for the full sample and for each of the four communities individually, stratified by neighbourhood deprivation and urban rural status.

•Provide a verified list of outlets to be visited and observed as part of the discreet audit of all retailers in each community (see below). Annual auditing of retail outlets (see below) will maintain the accuracy of the number and rate of outlets selling tobacco in each community over the study period.

2. Annual tobacco advertising and marketing audits

As with the mapping studies, the tobacco advertising and marketing audits focus on supermarkets, off-licences, confectioners, tobacconists and newsagents; grocers (including licensed), petrol stations, and fish & chip shops. There are two parts to this study component:

i) Retailer Panel: A panel of 24 retailers (representing the main retail types) has been recruited from communities matched to our four main study areas in order to monitor POS displays and related marketing activity. We chose not to recruit the retailer panel from the main study area, in order to minimise the likelihood that the identity of the study areas was made public and thereby compromising the study integrity. Similarly, large supermarkets were excluded from the panel sample for the same reason. Each outlet was visited, at baseline (Feb-Apr 2013), to collect observational data on POS advertising and marketing strategies using an adapted version of the form developed to monitor the impact of the Tobacco Advertising and Promotion Act (TAPA) [16].

In addition to the in-store observations, in-depth interviews have also been conducted with retail managers/owners from each outlet. These were audio recorded and will be repeated annually to explore their views and experiences before, during and after the implementation of the POS ban, to assess changes from the retailer’s perspective, explore their experiences as they prepare to and eventually implement the POS ban, and identify any problems that arise and how retailers deal with these. Additionally, the data will enable us to understand how the nature of the sales process changes and examine how customers deal with a new procedure for asking for cigarettes. The interviews will also be used to explore under-age sales and the perceived impact of the legislation on proxy sales.

ii) Discreet Audit: The discreet audit includes all tobacco retail outlets in the study communities that fall into the six categories identified above. Baseline data (February to March 2013) were collected by experienced observers, who visited all outlets in pairs to record brief information on tobacco product availability and display. The brief information included data on the visibility and placement of tobacco products within the store; whether and how tobacco products are displayed; whether and how tobacco products are actively promoted for sale (both external and internal); branding of display units and pack sizes available; most prominent brand, if any; communication and visibility of pricing information; and tobacco control signage. The audits did not require retailer co-operation and observers devised techniques to accurately recall and unobtrusively record marketing and advertising information.

The discreet audit will be repeated annually until 2017. Additional visits were made to supermarkets as part of the discreet audit in May 2013 to assess immediate compliance with the legislation. In May 2015, similar visits will be made to all small shops affected in by the legislation, in order to assess compliance amongst smaller retailers. Data collected will be used to develop a metric for POS exposure with measures developed to assess location, size, proximity and visibility of displays from key reference points such as till-points, and entrance areas. Where appropriate, measures will be developed with the aid of visual prompts, for example to indicate the relative visibility of the display. It is anticipated that POS exposure will be affected by a number of factors including increased industry activity, particularly in the lead-up to full implementation in 2015, and by retailer non-compliance (e.g. delays in removing gantries or gantries being reused for other non-tobacco products) or poor implementation (e.g. leaving sales shutters open after a sale is made). As well as assessing exposure, the audit will also assess level of compliance with both the current and new point of sale legislation, along with any evidence of strategies used to circumvent the legislation.

Data governance requires that the identity of all retail sites audited and all panel participants approached to take part in an interview remain confidential. In line with these requirements all sites and participants have been assigned non-identifiable codes to retain anonymity. Identifiable data (e.g. participants, premise names and address details) are held on a separate database and will be linked to electronic data files using these non-identifiable codes. Technical reports, presentations and publications will ensure that no participants or retail premises can be identified.

3. Annual school surveys of secondary school pupils

The school survey has a repeat cross-sectional design with embedded cohorts (Additional file 1: Table S1). We hypothesise that implementation of a partial ban on POS adverting (larger retailers only) will have only a small impact on awareness and attitudes. In order to assess this assertion, baseline surveys of S2 (age 13) and S4 (age 15) pupils were conducted in each of the four study schools between February and March 2013. This survey will be repeated one year later. The impact of the Scottish partial POS ban on 13-and 15-year-olds will then be compared with the impact on a similar age group of the comprehensive POS ban in Ireland, where legislation was implemented simultaneously in both large and smaller retailers in 2011 [14].

To assess the impact on the implementation of POS legislation in smaller retailers in 2015, a second baseline survey will be conducted with all pupils (S1-6) from our study schools in February to March 2015, with repeat surveys conducted annually for two years post-implementation. This survey series will allow us to measure the impact of a comprehensive ban (supermarkets and smaller retailers) on POS advertising on behavioural outcomes including smoking incidence and prevalence, as well as on brand awareness and other attitudinal outcomes.

In all survey waves, after ‘opt-out’ consent has been provided by parents and pupils, data will be collected using an anonymous self-complete questionnaire administered by class teachers under exam conditions. The questionnaire contains questions on personal smoking behaviours and attitudes towards tobacco use as well as family and peers’ behaviours and attitudes, access to tobacco products, brand awareness and exposure to tobacco advertising. An additional School Level Questionnaire (SLQ) intended for the head teacher or deputy head teacher will be used to gather information on the characteristics, resources and health-promoting aspects of all the participating schools.

4. Annual focus group interviews with purposive samples of S2 and S4 school pupils.

At baseline in March 2013, 16 focus groups were conducted with S2 and S4 pupils in each study community. They were all single-sex groups, with between 3 and 9 participants and lasted between 30–50 minutes. Table 1 gives the sample structure. The focus groups were conducted one and two weeks after the school survey (so that the pupils’ discussions did not influence questionnaire responses) and audio-recorded with the permission of group participants. The topic guide included: general discussion about the community; leisure time activities; local smoking behaviours and cultures; access to tobacco products including direct, indirect/proxy and black-market; awareness of and views on tobacco promotion including point of sale, other direct marketing methods, packaging, branding; awareness and perceptions of the impact of the legislation; and views about preventing youth smoking.

**Table 1 T1:** Focus group sample structure

	**High deprivation**		**Medium/low deprivation**		**Total**
	S2	S4	S2	S4	
Urban	2	2	2	2	8
Semi-urban	2	2	2	2	8

Focus group participants were recruited with the help of teachers in the study schools, to include young people who are smokers or have regular contact with smoking, such as having smoking friends or living in a home with smoker(s). The aim was to include young people who are most at risk of becoming adult smokers. These recruitment methods have been used successfully in a recent study by one of the research team (AA) on young people’s sources of cigarettes [17]. We used ‘opt-out’ consent for pupils identified as potential focus group participants separate from but using a similar strategy to that used in the school survey phase.

The focus groups will be repeated annually until 2017 and will provide more detailed and nuanced contextual information and insights into young people’s experiences and perceptions.

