Focus group interviews will be fully transcribed and the data entered into the qualitative computer package NVivo, version 10. The data will be coded and will undergo inductive thematic analysis employing constant comparison to identify key themes, focussing on uncovering the social worlds of the participants, and examples of differing views and experiences. The findings will be used to interpret findings from the quantitative components, in particular, any differences associated with community deprivation or baseline availability of cigarettes, or baseline availability of cigarettes through retail and/or black-market sources. Findings from the focus groups will be reviewed annually in order to identify emergent issues that should be explored further in the school survey.

After each wave of data collection, quantitative and qualitative data will be synthesised using a multi-level approach. First, quantitative data from the mapping, retailer audit and school surveys will be synthesised (Synthesis 1) followed by a synthesis of qualitative data from the focus groups and additional qualitative data from other study components (Synthesis 2). The products of syntheses 1 and 2 will then be combined using a series of mixed methods matrices, which allow the juxtaposition of findings from the different components of the study. We will then use these to generate a narrative synthesis (Synthesis 3). The focus in Synthesis 3 will be on consistencies and contrasts in the data which will form the basis for short interim reports. Once data collection is complete, the synthesis of data across all the study waves will follow a similar process but the focus of the analyses will change over time.

Findings from our study will be placed in a broader context through comparison with national level data. In particular, we will compare levels of compliance in tobacco retail outlets in our study communities with national data collected by Trading Standards Officers. Using data from the national register of tobacco outlets, we will also compare the density (and changes in density) of outlets in the four study communities to all other communities across the country. In addition, findings about changes in availability and sources of cigarettes for under-age smokers for our study populations will be compared with national data available from the Scottish Adolescent Lifestyle and Substance Use Survey (SALSUS) [18].

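### Pupil exposure uses 1.5 km buffers around home, but outlets are mapped and audited only inside the school catchments, so counts and densities miss outlets just beyond the boundary

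*Protocol article*

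**What the plan says.** All references are to the protocol article.

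- **Area.** Methods/design states that "community is defined as the catchment areas of the secondary schools selected for study".
- **Outlet locations.** The mapping component reports: "Data (including address and full postcode) for all tobacco retailers in the study communities were extracted from the tobacco retailers register". The list was then "verified through field visits during which every street in the four communities was inspected".
- **Audit.** The marketing audit component says: "The discreet audit includes all tobacco retail outlets in the study communities that fall into the six categories identified above".
- **Pupil exposure.** The mapping component builds each pupil's measure from a weighted average of outlets in buffers around school and home, with "exposure index scores calculated for each retail outlet using baseline audit data". It adds: "Mean density estimates will be calculated for 1.5 km buffers around the school and home environment of each secondary school participant".
- **National data.** The Data analysis section begins a further comparison with "Using data from the national register of tobacco outlets". Its stated purpose is to set outlet density in the four communities against the rest of the country. Pupil buffers are not mentioned there.

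**The concern.** The outlet data stop at the catchment line, while the home buffer can reach 1.5 km past it. Nothing in the text adds a margin, trims the buffer and its area to the catchment, or corrects for edges. An outlet just across the line is therefore left out of a nearby pupil's count and density, although the pupil may pass it daily. The school buffer has the same problem if the school stands within 1.5 km of the boundary.

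This matters because pupil-level exposure carries much of the causal argument. The Discussion accepts that an uncontrolled before-and-after design threatens internal validity and offers a dose-response relationship as one of the main safeguards. Research questions 1, 2 and 5 rest on exposure or its change, and the mapping component stratifies exposure change by urban-rural status. The error varies with home location, so it is not a constant that drops out.

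**Working it through.** The document gives no figure for boundary coverage, so there is nothing to reproduce. I checked the scope of each step and then illustrated the size.

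**1. Scope of each step**

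| Step | Area stated |
|---|---|
| Register extraction | study communities |
| Street verification | four communities |
| Discreet audit | study communities |
| Outlet scores | baseline audit, so audited outlets only |
| Pupil density | 1.5 km around school and home |

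The first four share one boundary. The fifth crosses it for any home less than 1.5 km inside.

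**2. Size, as an illustration**

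Input from the document: buffer radius r = 1.5 km. Assumptions: circular catchment of radius R between 2 and 8 km, outlets evenly spread on both sides of the line, and homes evenly spread.

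For a home at distance d from the centre, the share of the buffer outside is f(d) = 1 − A(d)/(πr²). A = πr² when d ≤ R − r. Otherwise

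A = r²·arccos[(d² + r² − R²)/(2dr)] + R²·arccos[(d² + R² − r²)/(2dR)] − ½√[(−d+r+R)(d+r−R)(d−r+R)(d+r+R)].

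Example, R = 3 and a home on the boundary (d = 3): A = 2.25·arccos(0.25) + 9·arccos(0.875) − ½√75.94 = 2.97 + 4.55 − 4.36 = 3.16 km². The full buffer is 7.07 km², so f = 1 − 3.16/7.07 = 0.55.

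With even spread, d has density 2d/R², and the share of homes whose buffer crosses the line is 1 − ((R − 1.5)/R)². For R = 3 that is 1 − 0.25 = 75%.

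| R (km) | Buffers crossing | Mean share outside | Pupils with over a quarter outside | Share outside, home on boundary |
|---|---|---|---|---|
| 2 | 94% | 31% | 64% | 58% |
| 3 | 75% | 21% | 42% | 55% |
| 5 | 51% | 13% | 25% | 53% |
| 8 | 34% | 8% | 16% | 52% |

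**3. Sensitivity to where homes are**

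If homes cluster centrally (Gaussian with standard deviation R/2, cut at the boundary), the mean share outside falls to about 21%, 11%, 6% and 3% for R = 2, 3, 5 and 8. With a tighter cluster (density proportional to exp[−d²/(R/2)²]) it is about 14%, 5% and 2% for R = 2, 3 and 5. If no outlets lie beyond the line, the outlet loss is zero whatever the area.

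**4. Effect on a dose-response slope**

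Let true exposure be D, varying between pupils with squared coefficient of variation v, and recorded exposure D(1 − f), with D and f independent. If the outcome has slope 1 on true exposure, the slope on recorded exposure is v·m / [v·(m² + V) + V], where m = mean of (1 − f) and V = variance of f. For even spread and R = 2, m = 0.686 and V = 0.0326.

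- Log SD of D 0.15 (v = 0.0228): 0.0156/0.0440 = 0.35.
- Log SD of D 0.6 (v = 0.433): 0.297/0.251 = 1.19.

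For R = 3 the same two cases give 0.35 and 1.07. The slope can be flattened or steepened, and the document does not fix which.

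**The case against.** **This is detail an article leaves out.** The text never says that outlets beyond the line count as absent, and edge handling is a GIS matter that a fuller protocol might settle. This stands only in part. The article does state the scope of extraction, verification and audit, and it states the buffer. Those stated choices do not fit together.

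**The register could supply the missing locations.** True for density, which needs locations only, and it makes the repair cheap. But national register data are planned for comparing communities, not for pupil buffers, and the register holds no audit scores.

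**Change matters more than level.** The same catchments are audited at every wave, so a fixed omission largely cancels in proportional change. It does not cancel in absolute exposure or absolute change: if a share f is missed, recorded change is (1 − f) times true change, and f depends on home location. The school survey also measures exposure without buffers, and triangulation is planned. Both limit the damage to the study as a whole but do not mend this measure.

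**The illustration is unfavourable.** Evenly spread homes give larger figures than central clustering, and area is not outlets. This stands, and the range above reflects it.

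**Stronger readings.** A reader might infer that the dose-response slope is necessarily flattened; step 4 shows either direction is possible. A reader might infer that the audit-scored measure is also understated; an outlet missing from a weighted average is not a zero, so that bias can go either way. A reader might take the urban versus small-town comparison as certainly distorted; that depends on outlets beyond each boundary, which the document does not describe.

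**Conclusion.** The mismatch is real. As written, outlet counts and densities are understated for pupils near a catchment boundary wherever outlets lie just beyond it. The audit-scored average may be biased in either direction. The error varies with home location, so it can distort the dose-response analysis and the urban versus small-town comparison, but no direction can be stated from the document.

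The true size is unknown because no catchment areas, home locations or outlet locations are given. For circular catchments of 2 to 8 km radius, the mean share of the home buffer outside runs from about 31% down to 8% with evenly spread homes, and from about 21% down to 3% with homes clustered as in the first case of step 3. It could be near zero in outlet terms around a town with open land on all sides. The point should be addressed; confidence in its practical size is moderate at best.

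**What to change.** - **Density measures.** At every wave, extract register outlets for each catchment plus a 1.5 km margin and compute buffer density on that set. For every pupil living inside the catchment, no part of the home buffer then falls outside the mapped area. The register is already in use and a national comparison of changes in density is already planned, so the cost is a wider extract and a GIS rerun.
- **Audit-scored measure.** Repeat the analysis in pupils whose home buffer lies wholly inside the catchment and report it beside the full-sample result. This needs no new data.
- **Optional.** As a further sensitivity analysis, give margin outlets a score imputed by outlet type, community and wave. The pre-ban baseline audit cannot now be made for them.

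Downside: margin outlets are neither field-verified nor audited, and the restricted analysis uses fewer pupils. In the even-spread illustration only 6% of homes would qualify at R = 2 km (100 − 94) and 25% at 3 km (100 − 75), so the number retained should be reported.
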